### Outcome Measures

Figure 2 shows the study timeline. As detailed below, all outcome measurements, along with drug administration and collection, will be documented from baseline to the conclusion of treatment.

**Figure 2. F2:**
[figure not shown]
Timeline for trial enrollment, intervention, and assessments. ALP: alkaline phosphatase; ALT: alanine aminotransferase; AST: aspartate aminotransferase; Cr: creatinine; DBIL: direct bilirubin; DLQI: Dermatology Life Quality Index; HECSI: Hand Eczema Severity Index; IGA: investigator global assessment; NRS: numerical rating scale; POEM: Patient-Oriented Eczema Measure; TBIL: total bilirubin; γ-GGT: gamma-Glutamyl transferase.

### Primary Outcomes

#### Hand Eczema Severity Index

Hand Eczema Severity Index (HECSI) serves as a global standard for assessing the severity of skin lesions, facilitating a quantitative description of the clinical manifestations of hand eczema and enabling the monitoring of treatment outcomes [29]. The HECSI scoring system categorizes each hand into 5 distinct regions, such as fingertip, fingers (excluding the fingertips), palm, back of the hand, and wrist. Skin lesions are categorized as erythema (E), papules (I), scales (S), and fissures (F). Areas are assessed based on the intensity of skin lesions, with points allocated for no lesions (0), mild alterations (1), moderate alterations (2), and severe alterations (3). The total lesion area of both hands is assessed as follows: no involvement is assigned a score of 0. For involvement between 1% and 25%, the score is 1. Involvement between 26% and 50% is scored as 2, while involvement between 51% and 75% corresponds to a score of 3, and 76% to 100% corresponds to a score of 4. The total HECSI score is derived from the aggregate of scores for each site, specifically the sum of the lesion scores, which is then multiplied by the lesion area score. The score categorizes hand eczema into 3 classifications, including mild (0‐11 points), moderate (12‐27 points), and severe (≥28 points).

#### The Numerical Rating Scale

The numerical rating scale (NRS) is a horizontal line segment akin to the Visual Analog Scale, generally anchored at one end as “no itching” and at the other as “extremely itchy” or “the worst itching ever experienced,” with the end points marked as “0” and “10,” respectively. A score of 0 indicates the absence of itching while a score of 10 signifies the highest level of itching possible. A higher score indicates increased severity of itching. Patients report a numerical value reflecting the average intensity of itching experienced over the preceding 24 hours or the past week. Itching severity is categorized as no itching (score 0), mild itching (0<score <4), moderate itching (4≤ score <7), severe itching (7≤ score <9), and very severe itching (score ≥9).

### Secondary Outcomes

#### The Target Lesion Area Score

This experiment focuses exclusively on hand lesions; thus, a single representative lesion is chosen as the target lesion. The lesion area will be assessed prior to treatment and after the trial. The percentage reduction in area will be determined from the measurements and used for comparative analysis.

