**Methods:**

This study is a clinical trial characterized as randomized, double-blind, double-dummy, and positive drug-controlled. A total of 122 patients diagnosed with CHE have been randomized and allocated in a 1:1 ratio into 2 distinct groups, with one receiving the intervention and the other serving as the control. Participants in the intervention group will receive RZZYL granules along with a placebo cream of mometasone furoate, whereas the control group will get mometasone furoate cream in combination with a placebo for RZZYL granule. Both groups will be treated with either the active drug or a placebo for 4 weeks. The primary outcome metrics are the Hand Eczema Severity Index (HECSI) and the Numerical Rating Scales (NRS). Secondary outcome metrics consist of the target lesion area score, the Patient-Oriented Eczema Measure (POEM), the Dermatology Life Quality Index (DLQI), and the Investigator Global Assessment (IGA). The outcomes will be assessed at the start of the study and again at 2 and 4 weeks after the treatment period.

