### Data Analyses

The results of this trial will be analyzed from three perspectives:

Full Analysis Set (Intention-to-Treat Analysis): This set includes all randomized participants, with data analyzed according to the principle of “randomization equals analysis.” Missing data will be addressed using multiple imputation methods. Predictive mean matching will be used for continuous variables while logistic regression imputation will be used for categorical variables.Per Protocol Set: This set comprises participants who meet specific criteria; that is, they must have completed at least 80% of the treatment regimen (ie, a minimum of 22 days of medication within 4 weeks), have not used prohibited study drugs, and possess complete data for the primary end point (HECSI score).Safety Set: This set includes all participants who received at least 1 dose of the study medication.

The variable processing and statistical methods for this trial are outlined as follows: (1) continuous variable data that adhere to a normal distribution will be presented as mean (SD). Independent sample *t* tests (2-tailed approach) will facilitate between-group comparisons while repeated measures ANOVA will be applied for comparisons across multiple time points (eg, baseline, during treatment, and post treatment); (2) data that do not conform to a normal distribution will be expressed as median (IQR), with between-group comparisons executed using the Mann-Whitney *U* test; (3) categorical data will be described in terms of proportions or percentages, with between-group comparisons conducted using chi-square tests or Fisher exact test, depending on the final sample size. (4) All data processing and chart generation will be performed using R 4.0 software (R Project for Statistical Computing). Statistical tests will be 2-sided, with a significance level at *P*<.05.

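### The target lesion area has two measurement times in its own section but three in the abstract, and its percentage reduction is compared without adjusting for baseline area

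*Protocol article*

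**What the plan says.** **Timing.** The abstract's Methods paragraph names the outcome: "Secondary outcome metrics consist of the target lesion area score, the Patient-Oriented Eczema Measure (POEM". It then gives one schedule with no exception: "The outcomes will be assessed at the start of the study and again at 2 and 4 weeks after the treatment period". I read this as weeks 2 and 4 of the 4-week treatment, which fits the biweekly dispensing and the week-4 follow-up in the Intervention section. The section on the target lesion area score says instead: "The lesion area will be assessed prior to treatment and after the trial".

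**Variable compared.** The same section fixes the percentage reduction of one representative lesion: "The percentage reduction in area will be determined from the measurements and used for comparative analysis".

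**Analysis.** Under Data Analyses, normally distributed data get a t test: "Independent sample *t* tests (2-tailed approach) will facilitate between-group comparisons". Otherwise "data that do not conform to a normal distribution will be expressed as median (IQR"), with a Mann-Whitney test. No baseline covariate is named. On missing values: "Missing data will be addressed using multiple imputation methods", by predictive mean matching for continuous variables.

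**The concern.** There are two separate issues.

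First, the abstract and the outcome section cannot both be followed. Staff who follow the outcome section will take no area at week 2. For a patient who leaves between weeks 2 and 4, nothing then shows how that lesion responded to treatment.

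Second, percentage reduction divides by baseline area but does not adjust for it. The division removes the influence of baseline only if week-4 area is proportional to baseline area. With a single lesion, measurement error and regression to the mean make strict proportionality unlikely. What remains is noise related to baseline, which a covariate already in hand would remove. The possible loss is power and precision for this secondary outcome.

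**Working it through.** **1. The schedule, side by side**

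| Place | Measurement times for target lesion area |
|---|---|
| Abstract, Methods | 3: baseline, week 2, week 4 |
| The Target Lesion Area Score | 2: before treatment, after the trial |

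If the abstract is taken literally, as 2 and 4 weeks after treatment ends, the count is still three against two.

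**2. Patients available**

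The plan's own sample size comes first. Inputs from the Sample Size section: control rate 0.53, experimental rate 0.7347, margin 0.095, z values 1.95996 and 1.28155.

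- Variance term: 0.53×0.47 + 0.7347×0.2653 = 0.4440
- Denominator: (0.53 − 0.7347 − 0.095)² = 0.0898
- n = (1.95996 + 1.28155)² × 0.4440 / 0.0898 = 51.9, so 52 per arm against 53 stated, which agrees closely
- 53 × 1.15 = 60.95, the stated 61 per arm, 122 in total

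This size rests on a responder rate and not on lesion area, so no stated figure is wrong for this outcome. Evaluable patients: 61 × 0.85 = 51.85, about 52 per arm. Attrition: 0.15 × 122 = 18.3, so about 18 patients could lack the second area. This is an upper bound on those a week-2 area would help, because patients who leave before week 2 would have none either.

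**3. Cost of not adjusting for baseline**

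The document gives no spread, distribution, baseline correlation or clearance rate for area, so everything here is assumed. Common basis: log-normal areas, two-sided 5% tests, 52 or 53 per arm.

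*Few lesions cleared.* With baseline log SD 0.8, residual log SD 0.5 to 0.8 and 1–7% cleared, the planned rule (t test or Mann-Whitney) on percentage reduction compares with a model of log area adjusted for log baseline as follows:

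| Slope of log week-4 on log baseline area | Planned rule | Adjusted log area |
|---|---|---|
| 0.9 | 87% | 88–90% |
| 0.75 | 82–86% | 88–90% |
| 0.6 | 76–83% | 88–90% |

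A second simulation with no clearance and log SD 0.7 gave Mann-Whitney 61% against 82% at correlation 0.3, and 76% against 79% at 0.9. Both simulations show a loss that shrinks as week-4 area tracks baseline area more closely.

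*More lesions cleared.* With baseline log SD 0.8, residual 0.6, slope 0.75, log effect 0.4 and constant 0.5:

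| Clearance | Mann-Whitney on percentage reduction | Adjusted log area |
|---|---|---|
| about 1% | 88% | 91% |
| 20% in both arms, at random | 51% | 28% |
| 20% v 30%, at random | 76% | 63% |
| about 21%, by area threshold | 83% | 83% |

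With 10–25% cleared at random, the log model loses about 10–27 points. With 1–3% cleared, it gains about 1–7.

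*Rank analysis of percentage reduction adjusted for baseline area.* Across these settings it was never more than about 1 point worse than Mann-Whitney and gained up to about 6. I repeated this in ten settings (52 per arm, 1,500 trials each, baseline log SD 0.8). The gain was 0 to about 3 points in nine of them. In the tenth (slope 0.6, residual log SD 0.5) power was 76% against 88%. So 6 points is typical of the upper end but is not a ceiling.

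**The case against.** **The abstract is a summary.** It gives one sentence for six outcomes, the outcome section is the specific rule, and the Figure 2 timeline, which is not shown here, may settle the matter. This is fair as to weight. Whatever the figure says, the two texts still disagree and one must change.

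**Imputation.** A reader might infer that a missing week-4 area must be filled from baseline area alone. The document does not say so. Data Analyses does not restrict the predictors, and by the abstract HECSI, NRS, POEM, DLQI and IGA are all taken at week 2. Early leavers also stay in the full analysis set. What is missing is the on-treatment area itself, usually the most direct predictor.

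**A misleading mean.** A reader might point to lesions going from 20 to 0, 10 to 0 and 1 to 3 cm². The mean reduction is (100 + 100 − 200)/3 = 0%, while total area falls from 31 to 3, or 90%. But the plan reports medians and uses Mann-Whitney for non-normal data, and the median here is +100%. The lesion sizes are also invented. The example does not show that the planned report would mislead.

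**Replacing the variable with log area.** A reader might infer that log area should be primary. Step 3 shows that this depends on an unknown clearance rate and an arbitrary constant, and can cost far more than it gains. This objection stands in full against log area, but not against adjusting for baseline by a rank-based method.

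**Materiality.** This is one secondary outcome with no stated power, and type I error was not inflated in the simulation (4.2% to 5.9%). That stands and limits the importance of the point.

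**Conclusion.** The schedule conflict is certain from the text: three measurement times against two. Its consequence is limited: at most about 18 of 122 patients would lack an on-treatment area to inform imputation, and they are not lost from the analysis.

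The unadjusted comparison is a weaker choice than the collected data allow. The loss against a baseline-adjusted rank analysis runs from almost none to about 6 points of power in the main settings, and was about 12 points in one where week-4 area depended less on baseline. These sizes rest wholly on assumed log-normal areas, so only the direction should be relied on. The primary outcomes, the sample size and the validity of the tests are untouched.

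**What to change.** 1. Reconcile the abstract and the target lesion section: measure the target lesion at baseline, week 2 and week 4, and make the study timeline match.
2. Include the week-2 area in the multiple imputation model, alongside baseline area and the other week-2 scores.
3. Make the between-group comparison adjust for baseline area by a method that tolerates cleared lesions, such as a rank-based or ordinal analysis with baseline area as covariate. Report an effect estimate with its 95% CI; an ordinal model gives one directly.
4. Keep percentage reduction as the clinical description. Use log area plus a constant only as a sensitivity analysis, with the constant fixed in advance.

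**Cost.** One more area measurement at an existing visit, and a slightly less familiar analysis. The Results section reports 40 patients recruited by 1 July 2025. Any week-2 areas not taken for them cannot be recovered and would be treated as missing. The analysis can still be changed without knowledge of results as long as the data remain blinded.

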#### Patient-Oriented Eczema Measure

The Patient-Oriented Eczema Measure (POEM) scoring scale has 7 questions that assess the severity of hand eczema symptoms experienced last week. Each question is scored on the basis of frequency or severity in the range of 0 to 4 points. The total score is the sum of all individual scores. Scores can range from 0 to 28 points. A more severe score denotes a greater severity of eczema symptoms and a more substantial impact on the patient’s quality of life.

#### Dermatology Life Quality Index

The Dermatology Life Quality Index (DLQI) measures the quality of life of patients with skin diseases. It measures both the symptoms and the impact of the skin disease on the patient’s everyday activities. This scale has a total of 10 questions regarding the patient’s life in the last week. These are emotional, professional, and social experiences. The scoring for each question is done on a scale of 0-3; the higher the score, the greater the impact of the condition on the quality of life of the person. The total score is the total of all individual responses. For this score, the higher the score, the worse the patient’s quality of life.

#### Investigator Global Assessment

Researchers and clinicians use the Investigator Global Assessment (IGA) score to gauge a patient’s skin condition. The score is often used in clinical trials for eczema and other skin diseases. Rating the severity of a disease depends on the characteristics of skin lesions, such as redness, exudation, and thickness. The dermatological revised scoring system works on a 5-point scale, ranging from 0 to 4, where higher scores indicate more severe skin conditions.

### Safety Assessment

Safety indicators will be evaluated through the subsequent assessments:

General physical examination: The patient’s general condition and basic vital signs (body temperature, blood pressure, pulse, and heart rate) will be monitored and recorded both prior to and following enrollment. The participants’ health status will be assessed to determine eligibility for the trial and monitor health changes throughout the trial.Laboratory assessments: At allocation and after 4 weeks of treatment, the assessments that will be conducted are blood routine, urine routine, alanine aminotransferase, aspartate aminotransferase, gamma-glutamyl transferase, total bilirubin, direct bilirubin, alkaline phosphatase, creatinine, urea, and electrocardiogram.Evaluation of skin irritation: Skin erythema, blisters, dryness, scaling, pigmentation changes, tightness, and itching will be assessed and documented at allocation and after a 4-week treatment period.

During each visit to the trial, adverse events were recorded in the participant’s pathological report form. If required, all serious adverse events and unanticipated events should be immediately reported to the Guang’anmen Hospital Ethics Committee and relevant authorities. If the injury assessment confirms that the injury caused by the research is related to the trial, the treatment and compensation costs will be borne by Guang’anmen Hospital of the China Academy of Chinese Medical Sciences. If there is a significant change in the research protocol related to the participant or a substantial increase in the related, it will be essential to resecure his informed consent. In addition, a committee will track participant safety and integrity of the study, called the Data and Safety Monitoring Committee (DSMC). The principal investigator will regularly assess all reported adverse events. Based on necessity, the principal investigator may call for a meeting with the research team to evaluate the risks and benefits. Scheduled interim analyses will be performed to monitor the study’s ongoing safety and amend the study protocol if necessary.

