## Abstract

**Background:**

Chronic hand eczema (CHE) is a prevalent inflammatory skin disease in clinical practice. Guidelines recommend the use of topical medications, including corticosteroids and calcineurin inhibitors; however, prolonged use of these drugs may result in adverse effects, such as skin atrophy, drug tolerance, and rebound phenomena. Moreover, these medications exhibit limited efficacy in managing chronic hypertrophic hand eczema. Traditional Chinese medicine (TCM) has a long history of treating patients. The Runzaozhiyang lotion (RZZYL) is often used in the Department of Dermatology of Guang'anmen Hospital, China Academy of Chinese Medical Sciences, for these patients, with marked efficacy on symptoms, keratinization, hypertrophy, and pruritus improvements. Nonetheless, there is still no high-quality evidence from evidence-based medicine to prove the effectiveness and safety of CHE treatment.

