**Objective:**

This study aimed to examine the efficacy and safety of a classic Chinese herbal prescription, RZZYL, for CHE and to provide a different treatment option for patients with hand eczema who are resistant to conventional Western pharmaceutical treatments.

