## Introduction

Eczema is a type of inflammatory disorder that affects the dermis and epidermis. It is caused by both internal and environmental factors. This prevalent clinical condition is categorized into acute, subacute, and chronic eczema according to its progression and clinical features. The hands are a common site for the onset of this condition. Chronic hand eczema is characterized by episodes that occur at least twice a year or persist for more than 3 months during each occurrence. Clinically, chronic hand eczema (CHE) is distinguished by dermal thickening, lichenification, hyperkeratosis, and pruritus [1]. CHE is highly prevalent in the general population, with studies worldwide reporting an incidence rate of 4.0% in the general population and up to 14.5% of individuals experiencing the condition throughout their lifetime [2]. This disorder has become a significant global public health issue in recent years.

At present, there are no medications sanctioned by the US Food and Drug Administration (FDA), specifically for CHE, and a significant unmet demand persists for effective treatments to attain long-term management of CHE [1]. Topical treatment is the conventional method for CHE, and topical corticosteroids (TCS) are the primary suggested therapy. Nevertheless, up to 65% of cases encounter recurrence, skin shrinkage, and other adverse outcomes post treatment, and no evidence indicates that TCS can achieve long-term management of CHE [3]. Calcineurin inhibitors, as an alternative to TCS, can be used for long-term maintenance therapy. These agents help regulate the immune system and reduce inflammation. However, their clinical efficacy in treating skin thickening and lesion-like changes remains suboptimal [4,5]. While some studies have demonstrated that crisaborole (a phosphodiesterase four inhibitor), delgocitinib [6], and ruxolitinib effectively treat hand eczema, large-scale clinical trials are still needed to confirm their efficacy and safety. Furthermore, the high costs associated with these medications impose a significant financial burden on patients [7]. Consequently, current treatment options for CHE in Western medicine remain limited, highlighting an urgent clinical need to identify alternative medications that specifically target the keratotic hyperplasia symptoms associated with CHE.

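### The structured skin check does not rate atrophy, and three of its seven items are also efficacy signs, so it only weakly supports a local-tolerability comparison with the steroid

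*Protocol article*

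**What the plan says.** Safety shares the objective with efficacy: "This study aimed to examine the efficacy and safety of a classic Chinese herbal prescription, RZZYL, for CHE". Under Safety Assessment, the skin irritation item is a closed list with fixed times: "Skin erythema, blisters, dryness, scaling, pigmentation changes, tightness, and itching will be assessed and documented at allocation and after a 4-week treatment period". The same section adds an open route: "During each visit to the trial, adverse events were recorded in the participant’s pathological report form".

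The rationale names atrophy twice. On topical medications, corticosteroids among them, the Abstract (Background) says "prolonged use of these drugs may result in adverse effects, such as skin atrophy, drug tolerance, and rebound phenomena". The Introduction says of topical corticosteroids that "up to 65% of cases encounter recurrence, skin shrinkage, and other adverse outcomes post treatment".

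Two primary outcomes score signs that are also on the skin list. For HECSI: "Skin lesions are categorized as erythema (E), papules (I), scales (S), and fissures (F". For the itch NRS: "A higher score indicates increased severity of itching".

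On exposure, the Abstract (Methods) says: "Both groups will be treated with either the active drug or a placebo for 4 weeks".

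**The concern.** The control arm receives a topical steroid, so this trial contains the arm in which atrophy could appear, yet no structured item asks about it. An analysis plan cannot recover a sign that nobody was asked to rate.

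The list also overlaps with efficacy. Patients enter with eczema, so many will have erythema, scaling or itching at allocation. If one treatment clears eczema better, its arm will show fewer of these signs at week 4, whatever its irritancy. Conversely, irritation from an effective product can be hidden by the improvement it brings.

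Finally, irritation that comes and goes before week 4 is missed by the structured rating. At stake is how much weight the safety half of the conclusion can bear when RZZYL is set beside mometasone. The primary efficacy comparison is not affected.

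**Working it through.** The plan gives no figure on this point, so there is none to reproduce. The core check sets the lists side by side.

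| Skin item | Also scored by HECSI or NRS, as the article describes them? |
|---|---|
| Erythema | Yes, HECSI |
| Scaling | Yes, HECSI |
| Itching | Yes, NRS |
| Blisters | No |
| Dryness | No |
| Pigmentation changes | No |
| Tightness | No |

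Overlap: 3 of 7. Atrophy: 0 of 7. The nearest thing elsewhere is thickness within the IGA, but that scale rates lesions and its higher scores mean worse disease, so it does not measure thinning. No other outcome or safety measure in the text covers atrophy. The two figures are not shown.

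**Timing.** The Abstract puts outcome assessments at 2 and 4 weeks, and the Intervention section has medication handed out every two weeks. I read this as a visit at week 2 of treatment. The skin list is not rated there.

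**How far efficacy alone could move an overlapping item (illustration).** Inputs from Sample Size: response 53% on mometasone and 73.47% on RZZYL. Assumption: a patient has a residual sign exactly when he or she is a non-responder.
- Residual signs: 1 − 0.53 = 0.470 and 1 − 0.7347 = 0.265. Difference: 0.2047.
- Chance of a two-sided P<.05: Φ{[0.2047 − 1.96·√(2·p̄·(1−p̄)/n)] / √[(0.47·0.53 + 0.2653·0.7347)/n]}, with p̄ = (0.47 + 0.2653)/2 = 0.3677.
- n = 53 per arm: (0.2047 − 0.1836)/0.0915 = 0.23, giving 0.59.
- n = 61 per arm: (0.2047 − 0.1711)/0.0853 = 0.39, giving 0.65.

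Under that assumption, a difference of about 20 points labelled as irritation would arise with no irritation in either arm.

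**What rating atrophy could yield.** The article gives no atrophy rate, so a range is used.
- No case seen in n patients: one-sided 95% upper limit = 1 − 0.05^(1/n). For n = 61 this is 4.8%; for n = 53, 5.5%.
- At least one case among 61 at an assumed 5% rate: 1 − 0.95^61 = 0.96.
- Between-arm Fisher test, 61 per arm, no case on RZZYL: 5 against 0 gives P = 2·C(61,5)/C(122,5) = 0.057, and 6 against 0 gives 0.027, so six cases are needed. Power is 0.08, 0.58 and 0.91 at assumed steroid-arm rates of 5%, 10% and 15%. With 53 per arm it is 0.05, 0.44 and 0.83.

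Rating atrophy would therefore bound its frequency, but would not give a dependable test between arms unless it is common.

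**The case against.** The strongest reply is that local safety is not left uncovered. Adverse events are recorded at every visit, including week 2. The comparison is randomized and double-blind, and Data Analyses defines a Safety Set and tests for categorical data. Because the list is rated at allocation, new or worsened signs can be derived, and the article does not say that raw week 4 values will be the measure. Grading and counting rules are commonly left to the full protocol or analysis plan, which are not shown. The Abstract ties atrophy to prolonged use, while treatment here lasts 4 weeks.

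All of this stands, and it rules out several stronger readings that a reader might infer:
- *The list mostly re-rates eczema.* The documents support 3 of 7. A majority needs dryness and blisters to be counted as eczema signs, which HECSI and the NRS as described do not do.
- *Local safety cannot be compared, or no data exist.* Blisters, dryness, pigmentation changes and tightness are rated with a baseline, and adverse events are collected under blinding.
- *Atrophy is the reason for the trial.* It is one of several, with tolerance, rebound, recurrence and limited efficacy in hypertrophic disease. The figure of up to 65% pools several outcomes and is not an atrophy rate.
- *The trial promises to show RZZYL is locally safer than the steroid.* No such claim is made; the design is noninferiority on efficacy.

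What the reply does not remove is that open recording is unsystematic. The absence of a report does not show that the skin was examined and found normal. Blinding does not remove the overlap either, because a real efficacy difference still shifts the shared items.

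**Conclusion.** The point holds in a limited form. The structured skin assessment does not systematically capture atrophy, one of several topical-steroid harms in the rationale, and 3 of its 7 items double as efficacy signs. A raw week 4 comparison of those three mixes irritation with residual eczema, so the checklist lends only weak support to a local-tolerability comparison. Open adverse-event recording fills the gap only in part.

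The closed list and its two rating times are stated in the article and carry the point; the absence of a counting rule does not. The 20-point illustration rests on the planned response rates and on equating a residual sign with non-response. The upper limits assume that every counted patient is examined. This is a worthwhile, low-cost improvement and not an error in the primary analysis.

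**What to change.** 1. Add a yes/no item for skin atrophy (thinning) to the existing checklist. Telangiectasia could be a second, optional item; the documents do not mention it, so that is for the sponsor's clinical judgement.
2. Rate the whole checklist at the week 2 visit as well as at allocation and week 4.
3. In the Safety Set, count a sign as local intolerance only when it is new or worse than at allocation. If the unshown analysis plan already says this, nothing more is needed here. The rule can use baselines already collected; if items are recorded only as present or absent, it reduces to new signs.
4. Report erythema, scaling and itching separately from the other items, since worsening on these three can still be uncontrolled eczema.
5. Present atrophy descriptively, with counts and upper limits, and not as a powered comparison.

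The cost is one or two form items and one extra rating at an existing visit. Few atrophy events are likely in 4 weeks. The 40 patients recruited by July 1, 2025 may lack a baseline for the new items. That leaves 122 − 40 = 82 (67%) who could have had one from that date, and fewer the later the change is made.
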